#### 2.6.2. Secondary Outcome Variables

The secondary outcomes in the study will be the change within groups and the differences between groups in standing postural control, the neuromuscular efficiency in superficial cervical flexor muscles, the CROM and PPT in the neck, and the attitude and thoughts in response to pain.

Standing Postural Control

Postural assessment was conducted with the subjects standing on a force platform (Kistler, model 9260AA6, Winterthur, Switzerland) following the recommendations of the systematic review published by Ruhe A. et al. to achieve acceptable to good reliability for most center of pressure (COP) parameters [105,106]. Data were sampled at 1000 Hz over 40 s in a standing position, and different parameters of COP excursions were analyzed (total sway area, antero-posterior and medio-lateral COP displacement, mean COP velocity, and antero-posterior and medio-lateral COP velocity) [105,106,107]. Participants were asked to stand upright with their arms by their sides and barefoot on the top of the platform in four different positions: (1) narrow stance (feet together) with open eyes, (2) narrow stance with closed eyes, (3) narrow stance on a spongy surface, with open eyes, (4) narrow stance on a spongy surface, with closed eyes. Participants will be required to maintain each position twice, and the second time was considered for the study [107,108].

Electromyography (EMG)—Cranio-cervical Flexion Test (CCFT)

To investigate the amplitude of the muscle activation, bipolar surface EMG signals were detected from the sternal head of the sternocleidomastoid (SCM) and anterior scalene (AS) muscles bilaterally during the CCFT in accordance with established protocols [83,109,110]. Pairs of Ag–AgCl electrodes (Ambu Neuroline; conductive area 28 mm^2^) were positioned 20 mm apart over the SCM and AS following skin preparation and using guidelines for electrode placement [111]. EMG signals were amplified as bipolar derivations (EMG amplifier; LISiN-OT Bioelettronica, Torino, Italy), band-pass filtered (−3 dB bandwidth, 10–500 Hz), sampled at a rate of 2048 samples/s, and converted to digital data by a 12-bit analog-to-digital (A/D) converter board. The reference electrode (wet wrist strap, WS1, LISiN-OT Bioelettronica) was placed around the wrist, over the ulna and radius styloid processes. Subjects were comfortably positioned in a supine position, lying with the head and neck in a mid-position, and were instructed to perform a cranio-cervical flexion action (anatomical action of the DCF). The task consisted of five incremental movements of increasing cranio-cervical flexion ranges of motion. Performance was guided by visual feedback from an air-filled pressure sensor (Stabilizer, Chattanooga Group Inc., Austin, TX, USA), which will be placed in the suboccipital region, behind the subject’s neck, and inflated to a baseline pressure of 20 mmHg (Figure 4) [24,83,107]. The pressure sensor monitors the slight flattening of the neck, which occurs, with the contraction of the longus capitis and longus colli muscles [112]. During the test, subjects were required to perform the gentle nodding motions of cranio-cervical flexion, progressing in range to increase the pressure by five incremental levels, with each increment representing 2 mmHg (22–30 mmHg). Subjects practiced targeting the five test levels between 22 and 30 mmHg in two practice trials before the electrodes were applied. Following the application of electrodes, participants will perform a standardized maneuver for EMG normalization (reference voluntary contraction) [24]. This reference voluntary contraction involved a head lift (cervical and cranio-cervical flexion) just clear of the bed, which was maintained for 10 s, during which EMG data are recorded [24]. A 1-min rest period was given before participants perform the experimental CCFT and EMG data are recorded. The experimental CCFT will include all five stages of the test (22–30 mmHg), with participants instructed to maintain steady pressure on each stage target for 10 s, and rest for 30 s between stages. For each of the incremental pressure levels, recording of EMG data commenced when the assessor observes that the participant has reached the pressure target. A consistent starting point for each level was attained by ensuring the participant has returned to the neutral head/neck position, which corresponds to the pressure level reading of 20 mmHg. The average rectified value (ARV) was computed offline from the EMG signals in intervals of 1s. The ARV values were then averaged and normalized with respect to the ARV computed from the reference voluntary contraction and expressed as a percentage [113].

Cervical mobility

A range of motion instrument was used to determine cervical spine movements (CROM Deluxe, Performance Attainment Associates, Roseville, Minnesota, United States). This device consists of an instrument placed over the head that determines the degree of cervical flexion, extension, inclination, and rotation. The evaluation was conducted in a sitting position, and the average of three measures for each direction considered. The CROM has been shown to have excellent test–retest reliability (ICCs = 0.89–0.98) and high validity (r with Fastrak motion analysis system = 0.93–0.98) [114].

Cervical Pressure Pain Threshold (PPT)

The PPT was recorded using a calibrated digital algometer (Force Ten™ -Model FDX; Wagner, Greenwich, CT, USA) with a round tip surface area of 1 cm^2^. This device quantified the threshold of pain to pressure (kgf) referenced by subjects at evaluation points [107]. The assessor gradually increased the pressure over these points bilaterally, in the posterior cervical spine at the level of the second (C2) and sixth (C6) vertebrae (prone position), upper trapezius muscle (sitting position), and over the tibialis anterior muscle (supine position) [115,116,117,118]. The test was repeated three times at each point and the average was considered, until the patient indicates when the pain or discomfort appears [119]. The algometry measurement of PPT has been shown to have excellent test–retest reliability (ICC = 0.91; 95% CI 0.82–0.97) [119].

Attitude to pain

To evaluate attitude and thoughts in response to pain, we will assess kinesiophobia and pain catastrophizing:Tampa Scale of Kinesiophobia (TSK)

Kinesiophobia will be measured using the Portuguese version of the 13-item Tampa Scale of Kinesiophobia (TSK-13-PT) that evaluates the fear of movement and reinjury [120]. This questionnaire contains 13 questions, each of which are scored from 1 to 4. Total scores range from 13 to 52, with a higher score indicating higher levels of kinesiophobia, and it can be categorized into four intensity ranges: “subclinical” (13–22); “mild” (23–32); “moderate” (33–42); and “severe” (43–52) [121]. The Cronbach alpha of 0.82 indicated good internal consistency of the TSK-13-PT total score, and the 1-week ICC of 0.99 indicated exceptional test–retest reliability [120].

2.Pain Catastrophizing Scale (PCS)

To evaluate the tendency to magnify the threat value of a pain stimulus and to feel helpless in the presence of pain, we will use the Brazilian Portuguese version of the PCS (BP-PCS) [122]. This scale is composed of 13 statements, and participants are prompted to describe the frequency with which they experience different thoughts and feelings associated with pain using 5-point scales with the extreme points (0) not at all and (4) all the time. The 13 statements are grouped into three subscales: rumination (4 items), magnification (3 items), and helplessness (6 items). Total score ranges from 0 to 52 and higher scores are indicative of higher catastrophic thinking [123,124]. The BP-PCS demonstrated good internal consistency (Cronbach α = 0.91) for the total score (Cronbach’s α = 0.91), and also good internal consistency with 0.93 (helplessness), 0.88 (magnification), and 0.86 (rumination) for the respective subdomains [122]. The item-total correlation coefficients ranged from 0.91 to 0.94 [122].

### 2.7. Patient and Public Involvement

Patients and other members of the public were involved in the design and management of the clinical trial and will be involved in conducting the trial. Firstly, we organized a public meeting for workers of the Polytechnic Institute of Guarda and people of the community of Guarda interested in the purpose of the clinical trial, where they could contribute with opinions and inputs for the study. Once the trial has been published, we also intend to disseminate the main results to trial participants and will seek to develop an appropriate method of dissemination to the general population.

### 2.8. Statistical Analysis

Data were analyzed by using the IBM-SPSS software package (version 23.0). Descriptive data analysis was reported by groups as means ± standard deviation for numeric variables and as frequencies and percentages for categorical variables. In the graphical representation, bar graphs by groups were used for numeric variables, and pie charts were used to represent categorical variables. The main change from baseline to 4 weeks of treatment will be calculated using an intention-to-treat analysis for each outcome measure.

Two-way repeated measures ANOVA were performed. Group factors, as age range, were considered as categorical variables in the statistical model, such as potential covariates, and the Time factor will be used to take into account the two pre-intervention (baseline) and the intermediate and final data in the intervention (2 and 4 weeks of treatment). The interaction between the two factors on the dependent variables was analyzed. When the interaction was statically significant, follow-up tests (post-hoc Sidak test) were performed to determine how the within-participant factors affected the dependent variables, and it could be used as a covariate in the model. The post-hoc Sidak test was calculated to determine which pairs of means have significant differences.

Correlations with Pearson’s r coefficient were determined to analyze whether the values of two or more numeric variables change in conjunction or are related at some time point of the study.

The level of significance for the statistical tests were set at *p* ≤ 0.05 with a confidence interval of 95%.

In order to focus on clinical relevance or clinically worthwhile effects, and assess the magnitude of the change in the result variables, the effect size of both treatments for the group × time repeated-measures ANOVA model were calculated as the partial eta squared (ŋp^2^) when significant, considering 0.01 small, 0.06 medium, and more than 0.14 large effect sizes, and we could use the Cohen d for any pairwise comparisons, when applicable.

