### 2.2. Participants, Recruitment and Sample Size Calculation

A sample of 62 women with CNSNP were recruited between 30 and 65 years old from the community in Guarda, Portugal. Participants were recruited through an online google form, with a questionnaire in Google Docs format, which was disseminated through social network postings (Facebook and Instagram) and the sending of institutional emails from Polytechnic Institute of Guarda to its workers. There were two physiotherapist assessors, who initially assessed participants that responded to the advertisements, and they were different from the physiotherapists who performed the interventions in both groups. In the first visit, the participants provided oral and written forms of all necessary information about the trial, including the study purpose and procedure. After voluntarily signing the informed consent statement, if through a detailed interview they met all inclusion, exclusion, and withdrawal criteria (Table 1), they enrolled into the trial to begin with an initial evaluation with the assessors.

The sample size calculation has been made based on the potential modification of the primary outcomes, neck pain intensity, and neck disability (NPRS and the NDI-PT) from baseline to final assessments. For repeated measurements of the estimated sample size, accepting an alpha risk of 0.05 and a beta risk of 0.2 in a two-sided test, 26 subjects were necessary in the first group and 26 in the second to recognize a statistically significant difference greater than or equal to 2 units (SD = 1.75) (NPRS) or 7 units (SD = 6) (NDI), and to detect small differences in standardized means between groups (Cohen’s d = 0.8), since the intervention with therapeutic exercise is known to have a beneficial effect and we want to assess whether the intervention with GPR has similar or even greater effects. Finally, considering a 15% loss rate during the study, and in order to end up with a sample of 52 subjects, based on the power analysis results, the final sample to be recruited was 62 subjects, 31 in each group. The sample size calculation was made with the software “PASS 15 (NCSS statistical software)” and “The R Project for Statistical Computing”.

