### 2.4. Procedures

Following the parameters of usual clinical practice and considering previous studies of GPR, according to some systematic reviews [55,92], and the protocols of STE in neck pain [54,93,94], the interventions were provided in eight sessions over a 4-week intervention period (two visits per week) accompanied by an individual daily at-home exercise program [64]. Baseline and follow-up assessments were conducted at the Polytechnic Institute of Guarda. There were four assessment points, and the time factor was considered in the statistical analysis with four levels. Initially, a test–retest reliability analysis was conducted on all participants to verify the variability between days. To achieve this, we applied two pre-intervention assessments, 1 week apart. After the second pre-intervention assessment, participants started the interventions in each group, and they will be assessed again in an intermediate evaluation after 2 weeks and four sessions of treatment (assessing only neck pain intensity, CROM, and cervical PPT outcomes) and in one last evaluation at the end of the intervention, 4 weeks and eight sessions of treatment (assessing all outcomes, such as in pre-intervention assessments). All data collected were confidential and private, ensuring anonymity of respondents. The participants were advised not to use other forms of treatment during the trial (pharmacologic or non-pharmacologic treatment). See the flow chart in Figure 1.

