**Withdrawal Criteria**
To use other forms of treatment during the trial (pharmacologic or non-pharmacologic treatment)

**Table 2 ijerph-18-10704-t002:** Description of home exercises.

GPR group	The subject practices an autoposture in lying position on the floor, it should be performed without pain and keeping the same breathing as what perform with the physical therapist in sessions. In supine position, with back stretched, flexion of hips and knees and closed legs, the participant exhale deeply. After some breathings the subject move the hips in a posterior pelvic tilt position and stretch the neck with a cranio-cervical flexion. The subject maintains the position with breathing in different angles of the arms in abduction.The subject needs to repeat the exercises during 15 min every day except in the days of presential session.
STE group	The subject performs neck exercises sitting in a chair (Flexion, extension, rotation and inclination slow movements and global stretches of the main muscle groups of the neck with the help of the hands (flexors, extensors and lateroflexors). 10 repetitions each movement and 20 s for each stretch. The execution of all exercises should take about 15 min, and each exercise should be performed without causing pain while maintaining a quiet breathing.

**Table 3 ijerph-18-10704-t003:** Description of exercise programs used in the interventions.

Modality	Description
Postural Global Reeducation [82]	At each session, patients will maintain two different lying postures and one standing (Figure 2): Stretching of the anterior muscular chain: patients will be positioned in the supine position and initiate flexion from the lower limbs and end with the extension of both hips and knees; Stretching of the posterior muscular chain: in a supine position, the progression includes hip flexion (90 degrees) and knee extension. For both postures, manual traction will be applied to both lumbar and cervical areas, and isometric contractions of the stiff muscles will be elicited to induce post-isometric relaxation. Integration Standing in the center: The final part of the treatment will be aimed to facilitate the integration of the postural correction into daily functional activities. During the global stretching session, care will be taken to avoid postural compensation (due to tension increase in response to muscular tightness) on specific body segments, and patients will maintain free breathing, with no breath holding.

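### Intention-to-treat is promised, but the named repeated-measures ANOVA and the withdrawal rule, followed as written, would tend to give a completer analysis

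*Protocol article*

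**What the plan says.** All places are in the protocol article.

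- **Analysis set (2.8).** The main change from baseline to 4 weeks "will be calculated using an intention-to-treat analysis for each outcome measure".
- **Model (2.8).** "Two-way repeated measures ANOVA were performed", with group and time as factors and Sidak post-hoc tests. The software is fixed: "Data were analyzed by using the IBM-SPSS software package (version 23.0". No other between-group model is named, and nothing is said about participants with incomplete data.
- **Time factor (2.4).** "the time factor was considered in the statistical analysis with four levels". The levels are two pre-intervention assessments, 2 weeks and 4 weeks.
- **Intermediate visit (2.4, repeated in 2.6).** This visit is limited: "assessing only neck pain intensity, CROM, and cervical PPT outcomes". The co-primary NDI is therefore not measured at 2 weeks.
- **Withdrawal (Table 1).** The single criterion is "To use other forms of treatment during the trial (pharmacologic or non-pharmacologic treatment". The article does not say whether withdrawn women are still assessed or analysed.
- **Planned loss (2.2).** The recruitment target was set "considering a 15% loss rate during the study, and in order to end up with a sample of 52 subjects".

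**The concern.** Intention-to-treat means that every randomised woman counts in the arm to which she was allocated. Classical repeated-measures ANOVA, as SPSS runs it by default, deletes listwise: a woman who lacks one level of the time factor loses all her data, including scores that were observed. The stated method therefore does not, by itself, deliver the stated analysis set.

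The withdrawal criterion makes this more than a matter of labelling. Starting a painkiller for the neck would meet it, and doing so plausibly signals poor response on pain, a primary outcome. The arms also differ in content and in session length (about 35 against 45 minutes, section 2.5), so equal withdrawal by arm cannot be taken for granted. Two things are at stake: the validity of the between-group contrast on NPRS and NDI, and some power.

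**Working it through.** **1. Reproduce the plan's own figure.** Inputs from section 2.2: "accepting an alpha risk of 0.05 and a beta risk of 0.2 in a two-sided test", Cohen's d = 0.8, 15% loss.

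- Two-sample t-test at d = 0.8: n = 25.52 per group, rounded up to 26, or 52 in total. This matches the plan.
- 52 / (1 − 0.15) = 61.2, rounded up to 62, or 31 per group. This also matches.

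The power target is thus met by the 52 women expected to remain.

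**2. Women left out at the planned loss.** 62 × 0.15 = 9.3. Counted from the target, 62 − 52 = 10, and 10/62 = 16.1%.

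**3. Power (two-sided t-test, alpha 0.05, d = 0.8).**

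| Analysed | Per group | Power |
|---|---|---|
| 62 | 31 | 87.3% |
| 52 | 26 | 80.7% |
| 44 | 22 | 73.6% |
| 40 | 20 | 69.3% |

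The 87.3% is a ceiling, because it needs a full set of values from all 62 women.

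**4. Scattered missed visits.** The article gives no missing rate per visit, so the rates below are assumptions, with visits missed independently. Expected complete cases = 62 × (1 − m)^k, where m is the missing rate per visit and k the number of levels analysed.

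| m | k = 3 | k = 4 |
|---|---|---|
| 2% | 58.4 | 57.2 |
| 5% | 53.2 | 50.5 |
| 10% | 45.2 | 40.7 |

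At 5% per visit over four levels, about 50 of 62 women would have complete data.

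**5. Co-primary NDI.** NDI has no 2-week value, so a four-level time factor cannot be fitted to it. Read literally, every woman would be incomplete. Read sensibly, NDI uses only the visits at which it is measured, and a missed 2-week visit removes nobody from that analysis.

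**6. Bias (illustration only).** Let women who leave improve D points less than those who stay, and let a share p leave an arm. The mean for all women in that arm is (1 − p)·m + p·(m − D) = m − pD, where m is the completer mean. Completers therefore look better by pD, and the contrast shifts by (p₁ − p₂)·D. Neither p by arm nor D is in the documents.

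- Difference in withdrawal of 20 percentage points, D = 2: 0.20 × 2 = 0.4 NPRS points.
- Difference of 10 points, D = 1 to 2: 0.1 to 0.2.
- Ten losses split 8 and 2, D = 2: (6/31) × 2 = 0.39.
- Split 10 and 0, D = 2: (10/31) × 2 = 0.65.
- Split 5 and 5, any D: 0.

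For scale, 0.4 is 20% of the 2-unit NPRS difference stated in section 2.2. It is 29% of 0.8 × 1.75 = 1.4 points, which is the difference implied by d = 0.8 with the stated SD.

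**The case against.** The strongest reply is that the article never says incomplete women are dropped. ITT and repeated-measures ANOVA fit together if missing values are imputed first, and an analysis plan that is not shown may say so. This stands as a limit on certainty. A reader might infer that the trial's result is a completer analysis, or that a published ITT label would be false; the documents do not establish either. What remains is that the article itself fixes a model and a withdrawal rule that need something added before they give the analysis set it promises.

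Other points on that side:

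- **The ITT sentence concerns the change from baseline to 4 weeks.** A missed 2-week visit does not remove anyone from that change. This is correct, but no separate between-group test is named for it; the ANOVA is the only one.
- **The 15% allowance contradicts nothing.** Agreed. It is ordinary sample-size inflation and defines no analysis set. It is used here only to show how many women might be affected.
- **The withdrawal criterion covers any treatment, not just treatment for the neck.** Agreed. A reader might infer that those withdrawn are non-responders. The text does not show that, and it does not say that data collection stops. Outcome-related loss is plausible, not demonstrated.
- **The bias figures are assumed.** Agreed. A reader might take 29% as the expected distortion; it is the most unfavourable of the percentage-point scenarios set against the smaller of two possible reference differences.
- **Timing.** Recruitment and the intervention are reported in the past tense and the post-intervention assessments in the future tense, so collecting further data may not be possible for every woman.

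**Conclusion.** The point holds as a mismatch between the promised analysis set and the stated method. Followed as written, with listwise deletion and no imputation, the analysis would tend to be a completer analysis. At the planned loss it would omit about 10 of 62 women (16%), with power of about 81% rather than at most 87% at d = 0.8.

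Bias in the contrast requires that withdrawal is related to outcome and differs by arm. Its size and direction cannot be derived from the documents: the illustrations run from about zero with balanced losses to 0.4 NPRS points for a 20-percentage-point difference with a 2-point gap, and 0.65 if all ten losses fall in one arm.

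This should be fixed, but it is not shown to invalidate the trial. Confidence is moderate, because an unseen analysis plan could already supply imputation or follow-up of withdrawn women.

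**What to change.** 1. **Model.** Replace the repeated-measures ANOVA in section 2.8 with a likelihood-based mixed model, available in the software already named. Include all randomised women by allocated group. Use each outcome's actual schedule after baseline: NPRS, CROM and PPT at 2 and 4 weeks; NDI and the other outcomes at 4 weeks only.
2. **Withdrawal.** Reconcile the Table 1 criterion with the ITT statement. Say that, where still possible, the scheduled outcomes of withdrawn women are collected and included, and that use of other treatment is recorded. This matters most for NDI: a woman without a 4-week NDI has no post-baseline NDI, so the model alone recovers little for her. Which treatments participants may use is for the investigators and is not at issue here.
3. **Sensitivity analysis.** The mixed model assumes that data are missing at random. Add one analysis that sets the missing 4-week scores of withdrawn women worse than the model predicts, for example by 1 and 2 NPRS points (an assumed range), with a corresponding shift chosen in advance for NDI.

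**Cost.** Revised wording, one extra analysis and, where assessments are still open, the scheduled measurements of the few women who would otherwise leave. If collection has closed, the model, the sensitivity analysis and the description of the analysis set can still be corrected. The small downside is that the estimates then include the effect of other treatment.

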### 2.5. Interventions

The interventions were conducted by an experienced physiotherapist with more than 7 years in the treatment of the musculoskeletal disorders with these interventions.

The interventions in both groups commenced after the second evaluation, which we considered the baseline assessment. The interventions in both groups were performed for 4 weeks, and they consisted of a combination of treatment sessions carried out by a physiotherapist and exercises to be performed at home. The physiotherapist performed two sessions per week [64] with the participants in each group, and participants were asked to practice their prescribed exercise program at home, depending the group, once daily for 4 weeks, and to complete an exercise diary to monitor compliance and record adverse events. Each session of treatment lasted approximately 35 min for the STE group and 45 min for the GPR group, according to clinical practice and previous studies [54,55,92,93,94]. The physical therapist taught and showed a detailed home exercise program for all participants, where the physiotherapist provided easy and simple home exercises without devices. Participants in GPR group performed at home one lying posture and the STE group prescribed active movements and stretches of the neck muscles (Table 2).

Participants assigned to the GPR group performed global postural exercises consisting of three positions, following the protocol of Lozano-Quijada C. et al. [82] (Figure 2). Initially, without gravity load, a lying posture was applied to the anterior muscle chain for approximately 15 min, then another lying posture to the posterior muscle chain for other 15 min, and finally the patients worked in a standing posture for postural integration under a gravity load for 5 min. Between each posture there was a short resting time.

Participants assigned to the STE group performed specific therapeutic exercises for motor control, divided into three phases, following the protocol of Jull G. et al. [54,93] and Sremakaew M. et al. [94]. Each of the phases had two exercises with visual feedback with a laser sensor (motion guidance: a laser pointer rehab tool that adds visual feedback for motor control during exercise in physical therapy) (Figure 3).

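### The planned repeated-measures ANOVA reaches the 4-week GPR v STE comparison only through post-hoc tests and names no baseline-score covariate, at some cost in power and focus but without bias

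*Protocol article*

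**What the plan says.** Section 2.8 names a two-way repeated-measures ANOVA. On its within-person factor it says that "the Time factor will be used to take into account the two pre-intervention (baseline) and the intermediate and final data in the intervention", and Section 2.4 confirms that time has four levels. If the group-by-time interaction is significant, Sidak tests compare pairs of means. On covariates Section 2.8 says: "Group factors, as age range, were considered as categorical variables in the statistical model, such as potential covariates". A further clause, conditional on a significant interaction, allows something to become a covariate, but its pronoun has no clear referent and it does not name the pre-treatment score.

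The quantity of interest appears in the same section as "The main change from baseline to 4 weeks of treatment".

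On what baseline means, Section 2.5 says: "The interventions in both groups commenced after the second evaluation, which we considered the baseline assessment". Section 2.6 likewise labels the second pre-intervention assessment as baseline, whereas Section 2.8 attaches the word to both. Section 2.4 gives test-retest reliability as the reason for measuring twice. Sections 2.4 and 2.6 limit the week-2 visit to pain intensity, CROM and PPT.

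**The concern.** The trial asks which exercise programme gives the greater improvement by 4 weeks. The planned test asks whether the group profiles differ in any way over time. If that test is not significant, no planned step isolates the 4-week comparison. If it is significant, the follow-up is a set of pairwise mean comparisons. Neither route gives one adjusted GPR minus STE difference with a confidence interval.

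Each participant's own pre-treatment score is measured twice and would normally be expected to predict the week-4 score well, yet it is not used as a covariate. Precision that is already paid for may therefore be left unused.

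Two internal inconsistencies follow from the same model. Disability (NDI), one of the two primary outcomes, is not measured at week 2, so a four-level Time factor cannot apply to it; it has three levels. And with baseline defined in two ways, the change from baseline to 4 weeks can be computed from the second pre-score or from both.

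**Working it through.** **Inputs from the protocol article (Section 2.2).** The error rates are "accepting an alpha risk of 0.05 and a beta risk of 0.2 in a two-sided test". The detectable effect includes "small differences in standardized means between groups (Cohen’s d = 0.8"). The evaluable size is "26 subjects were necessary in the first group and 26 in the second". The loss rate is 15%.

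**The plan's own figure.** A two-sample t-test with d = 0.8, two-sided alpha 0.05 and 26 per arm has power 0.807 (25 per arm gives 0.791), so 26 reproduces. Then 52 / 0.85 = 61.2, which gives 62 recruited. The sample size is therefore that of a simple two-group comparison at d = 0.8.

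**Assumptions not in the document.** Within-person correlation r between visits is taken as 0.3, 0.5 and 0.7, with compound symmetry. The only related figure is a test-retest r of 0.76 for the pain scale (Section 2.6.1). The group difference at week 4 is 0.8 of the cross-sectional SD. For pain, half of it (0.4) is present at week 2.

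**Planned interaction.** With group differences δ at T levels, in SD units, the test is a noncentral F with T − 1 and (2n − 2)(T − 1) df and noncentrality λ = (n/2) × Σ(δ − mean δ)² / (1 − r), where n/2 = 13.
- Pain: δ = (0, 0, 0.4, 0.8), mean 0.3, sum of squares 0.09 + 0.09 + 0.01 + 0.25 = 0.44. λ = 13 × 0.44 / (1 − r) = 8.17, 11.44, 19.07, with 3 and 150 df.
- NDI: δ = (0, 0, 0.8), mean 0.267, sum of squares 0.427. λ = 7.92, 11.09, 18.49, with 2 and 100 df.

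**ANCOVA of week 4 on the mean of the two pre-scores.** Residual variance is 1 − 2r²/(1 + r) = 0.862, 0.667, 0.424. The effective d is 0.8 divided by its square root = 0.862, 0.980, 1.229, tested with 49 df.

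| r | Interaction, pain | Interaction, NDI | ANCOVA |
|---|---|---|---|
| 0.3 | 0.65 | 0.70 | 0.86 |
| 0.5 | 0.81 | 0.84 | 0.93 |
| 0.7 | 0.96 | 0.97 | 0.99 |

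For comparison, an unadjusted change from the second pre-score has variance 2(1 − r) = 1.40, 1.00, 0.60 and power 0.67, 0.81, 0.95.

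**Checks.**
- Simulation at r = 0.5 (4,000 runs, Greenhouse-Geisser correction) gave 0.80 v 0.93 for pain.
- With a correlation of 0.76 between the two pre-scores and 0.5 between pre and post, it gave 0.78 v 0.92.
- Under no effect, rejection rates were 0.044 to 0.053 for the interaction and 0.047 to 0.054 for ANCOVA.

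**Sensitivity to the week-2 effect (pain).** With the full effect already present at week 2, the sum of squares is 4 × 0.16 = 0.64. The interaction then has power 0.83, 0.94 and 1.00 at r = 0.3, 0.5 and 0.7, against ANCOVA's 0.86, 0.93 and 0.99.

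**The case against.** A group-by-time repeated-measures ANOVA is valid and conventional. It keeps its type I error, and at r of about 0.5 or more it delivers roughly the 80% power that Section 2.2 promises. Under the same assumptions an ANCOVA gains only 2 to 3 points at r = 0.7. A separate analysis plan may add the baseline covariate, and Section 2.6.1 shows that between-group differences at the assessment times are intended. All of this stands, and it limits the size of the point. It does not remove it: the article itself fixes what Time contains and how the 4-week comparison is reached.

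Three stronger readings are tempting, and the documents do not support them.

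- **That the second pre-score is wasted, or costs power through extra degrees of freedom.** Keeping both pre-scores raises interaction power: at r = 0.5 it is 0.81 with four levels and 0.72 without the first pre-score for pain, and 0.84 v 0.81 for NDI. The first pre-score also has a stated use in the reliability analysis.
- **That a chance shift between the two pre-scores can make the test falsely significant.** That is ordinary type I error, and it stays near 0.05.
- **That power falls far below 80% as r rises.** This needs two things that the article does not set: a rule that success also requires a significant unadjusted week-4 difference, and d = 0.8 fixed on the change score. On that scale the week-4 effect is 0.8 × √(2(1 − r)), which shrinks from 0.88 SD at r = 0.4 to 0.62 SD at r = 0.7. Section 2.2 speaks of standardised means between groups, and on that scale the shortfall against ANCOVA narrows as r rises.

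**Conclusion.** The point holds as one of efficiency and focus. The planned model answers a broader question than the one posed, reaches the 4-week contrast only after a significant omnibus test, and yields no baseline-adjusted estimate. The four-level description does not fit NDI, and baseline has two meanings.

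The size depends on a correlation that the article does not give. Under the stated assumptions the power shortfall against ANCOVA is about 21 points for pain and 16 for NDI at r = 0.3, about 12 and 9 at r = 0.5, and 2 to 3 at r = 0.7. For pain it shrinks to about 4 points at r = 0.3, and disappears at r = 0.5 and above, if the full effect is present by week 2. Even then the interaction tests for any difference over time, not the difference at week 4. NDI has no week-2 score and cannot benefit. A reader might infer that the results would be biased; nothing in the documents or the simulations supports that.

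**What to change.** For each outcome, make the primary analysis a regression of the week-4 score on group, the mean of the two pre-intervention scores and age as a continuous variable. Report the adjusted GPR minus STE difference with its 95% CI. For pain, CROM and PPT, fit the 2- and 4-week visits in one mixed model (group by visit) with the same covariates and read the 4-week contrast.

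State one definition of baseline throughout. Use the pair of pre-scores separately for test-retest reliability. Remove the requirement for a significant interaction before the 4-week comparison, and the clause that lets a covariate enter after that result is seen. The ANOVA can stay as a secondary analysis, with three levels for outcomes that have no week-2 measurement.

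No new data, visits or participants are needed. The cost is procedural: recruitment is reported as done and parts of Section 2.8 are in the past tense, so the change must be documented and dated before the analyst is unmasked, or else disclosed as post hoc.
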